**Methods and design:**

This study is a randomised controlled trial with a delayed treatment design. Patients with a TMD (TMD pain screener ≥ 3 points) or oral parafunctions (such as clenching and bruxism), who are suffering from moderate to severe subjective tinnitus (Tinnitus Functional Index (TFI) between 25 and 90 points), will be recruited from the tertiary tinnitus clinic of the University Hospital of Antwerp, Edegem, Belgium.

Patients will be excluded in case of clear otological or neurological causes of the tinnitus, progressive middle ear pathology, intracranial pathology, traumatic cervical spine or temporomandibular injury in the past 6 months, severe depression as diagnosed by a psychologist, tumours, previous surgery in the orofacial area, substance abuse that may affect the outcome measures, any contra-indication for physical therapy treatment directed to the orofacial area or when they received TMD treatment in the past 2 months.

After screening for eligibility, baseline data among which scores on the TFI, tinnitus questionnaire (TQ), mean tinnitus loudness as measured with visual analogue scale (VAS), TMD pain screener, and a set of temporomandibular joint tests will be collected.

Patients will be randomised in an early-start group and in a delayed-start group of therapy by 9 weeks. Patients will receive conservative TMD treatment with a maximum of 18 sessions within 9 weeks. At baseline (week 0), at the start of therapy (weeks 0 or 9), 9 weeks after therapy (weeks 9 or 18), and at follow-up (weeks 18 or 27) data from the TFI, TQ, VAS mean tinnitus loudness and the TMD pain screener will be collected.

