#### Secondary outcome measures

Various secondary outcome measures will be measured and used to describe the population and identify possible mediating factors, i.e. factors that contribute to the therapeutic effect. An overview is presented in Table 2.

**Table 2 Tab2:** Overview of primary and secondary outcome measures

	Baseline	Follow-up	Measuring tool	Completed by
Primary outcome measure				
Tinnitus-related distress	X	X	Tinnitus Questionnaire	Patient
Secondary outcome measure				
TMJ pain	X	X	TMD pain screener	Patient
Myalgia	X	X	DC/TMD	Researcher
Arthralgia	X	X	DC/ TMD	Researcher
Pressure sensitivity	X	X	Pressure algometer (Somedic), kPa	Researcher
Mouth opening	X	X	Ruler, cm	Researcher
Hearing loss	X		Pure Tone audiometry Speech in noise test	Audiologist
Psychoacoustic tinnitus analysis	X	X	Type of tinnitus, tinnitus pitch and tinnitus loudness	Audiologist
Tinnitus severity	X		Tinnitus Functional Index	Patient
Subjective tinnitus loudness	X	X	Visual Analogue Scale (0–100 mm)	Patient
State of anxiety and depression	X		Hospital Anxiety and Depression Scale	Patient
Hyperacusis	X		Hyperacusis Questionnaire	Patient
Auditory event-related potential	X	X	Auditory event-related potential	Researcher
General tinnitus characteristics such as duration of the complaints, localisation (unilateral, bilateral, central), somatic modulation, temporal relation with TMD, bruxism periods	X		Medical history	ENT

*DC/TMD* Diagnostic criteria for temporomandibular disorders, *ENT* ear-nose-throat, *TMD* temporomandibular disorders, *TMJ* temporomandibular joint

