### Statistics

Our null hypothesis is that the change in TQ at week 9 is equal in both groups (early-start and delayed-start):

H_0_: Change in TQ-baseline to TQ-9 weeks (early start) = Change in TQ-baseline to TQ-9 weeks (delayed start).

The primary outcome is a change in the scores on the TQ after 9 weeks of treatment. The mean change in TQ score between baseline and 9-week (post treatment) scores will be calculated. This mean change in TQ of the early start group will be compared to the mean change in TQ of the delayed-start group that has not yet received treatment at this point. A difference between both groups will be defined as statistically significant when *p* < 0.05.

A repeated measures ANOVA and post-hoc tests will be used to compare the mean changes of the early-start group and delayed-start group at 9 weeks, and secondary at baseline, 18, and 27 weeks follow-up. The same cut-off point of *p* < 0.05 will be used here.

For the mediation analysis, the protocol described by Baron and Kenny [41] will be used to calculate the role of potential contributing factors in the obtained output. This implies the execution of three regression analyses. The first will assess the relation between the applied therapy (independent variable) and the outcome (dependent variable). The second will assess the relation between the applied therapy (independent) and a mediating factor to confirm that the applied treatment significantly affects the mediator. The third will be used to confirm that the mediator significantly predicts the treatment outcome (dependent variable), while controlling for the applied treatment (independent variable). Again, a cut-off point of *p* < 0.05 will be used.

Bootstrapping will be performed to avoid overestimation of the mediation effect. As potential mediating factors, all secondary outcome measures will be used.

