To improve the quality of patient care, it is important that clinicians are able to identify who has a high likelihood for a positive treatment effect and who is at risk of poor recovery. Therefore, we aim to identify prognostic indicators to provide arguments why someone might benefit from TMJ treatment or not. This can reduce the current trial and error strategy and thus avoid patient frustration and unnecessary reimbursement of unsuccessful therapies.

To date, no prognostic indicators are available for the effect of TMD treatment on tinnitus. However, an earlier study in cervicogenic somatic tinnitus showed that patients with low-pitched tinnitus, that co-varies with the neck complaints and increases during inadequate postures, has the best prognosis after cervical spine treatment [50]. Rollman et al. [51] studied a variety of prognostic indicators for TMD pain in general and found that a longer duration of the TMD-pain complaint, a higher number of attended care practitioners and higher degree of hindrance on function, negatively predicted 6-month improvement. It is unclear to what extent these prognostic indicators can be transferred to our population of patients with tinnitus as a main complaint; consequently, we aim to identify prognostic indicators for the effect of TMJ treatment on tinnitus.

To understand the working mechanism behind TMJ treatment for somatic tinnitus it is necessary to identify variables that have an effect on the main outcome variable (TQ). Knowing that a treatment is beneficial for patients is important, but knowing how it works adds to the understanding and acceptance of the findings among clinicians. Therefore, we also aim to identify possible mediating factors, i.e. factors that contribute to the therapeutic effect. The underlying idea is that TMJ contributes to somatic tinnitus. Consequently, variables that measure TMJ parameters are used as potential mediators; these are TMJ pain via the TMD pain screener, pain sensitivity as measured via PPT and mouth opening.

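### The mediation plan admits every secondary outcome as a candidate mediator, including variables recorded only before treatment, and conflicts with the shorter mediator list in the Discussion

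*Protocol article*

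**What the plan says.** The protocol article defines the set of candidate mediators twice.

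- **Statistics:** "As potential mediating factors, all secondary outcome measures will be used". This fits the opening of the section on secondary outcome measures, where these measures are to be "used to describe the population and identify possible mediating factors, i.e. factors that contribute to the therapeutic effect".
- **Discussion:** "Consequently, variables that measure TMJ parameters are used as potential mediators", followed by the list: "these are TMJ pain via the TMD pain screener, pain sensitivity as measured via PPT and mouth opening".

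The Statistics section sets out three Baron–Kenny regressions, each judged at p < 0.05: treatment on outcome, treatment on mediator, and mediator on outcome given treatment. It adds: "Bootstrapping will be performed to avoid overestimation of the mediation effect".

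Table 2 shows which secondary outcomes are measured at baseline and which also at follow-up. The Abstract (Methods and design) gives a questionnaire schedule covering the start of therapy, the end of therapy and follow-up, at which "data from the TFI, TQ, VAS mean tinnitus loudness and the TMD pain screener will be collected".

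**The concern.** The two lists cannot both be the plan. If the choice is left open, the set of mediators can be settled after the data are seen.

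The wider list also has a logical fault. A mediator must be something that treatment changes, and the second regression exists to show this. A variable recorded only before treatment cannot be changed by it, so a significant second regression can arise only from chance imbalance between the arms. Minimisation uses only sex and age (Randomisation procedure), so it does not directly balance the other baseline variables.

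A baseline variable that is imbalanced by chance and also predicts change in TQ would satisfy all three regressions and could be reported as a way in which the therapy works. The Background section keeps mediating factors and prognostic indicators apart as separate aims; this rule would merge them. The mediation analysis is also one of the reasons given under Sample size and power for recruiting 2 × 100 patients.

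**Working it through.** **Plan's own figure.** The only computed figure in the article is 37 per group for the primary TQ comparison (difference 8.72, SD 13.72, power 0.8, alpha 0.05, taken as two-sided). The normal formula gives n = 2 × (1.96 + 0.84)² × (13.72/8.72)² ≈ 39, which is within two patients of 37. The present point does not depend on it; 37 and 100 per group serve below only as sample-size settings.

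**Count of rows in Table 2.**

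| Marked at baseline and follow-up (8) | Marked at baseline only (5) |
|---|---|
| TMD pain screener, myalgia, arthralgia, pressure sensitivity, mouth opening, psychoacoustic analysis, VAS loudness, auditory event-related potential | Hearing loss, TFI, HADS, hyperacusis, general tinnitus characteristics |

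The TFI is uncertain. The Abstract lists it at later visits, whereas Table 2 marks it at baseline only and the Discussion says it will not serve to judge the treatment effect. If it is measured later, four rows are baseline-only. These are rows, not tests: HADS has two subscales and the last row holds several items, so the number of regressions could be larger.

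**Second regression alone.** Each baseline-only variable is truly unaffected by treatment, so each has a 5% chance of p < 0.05. Assuming independence, P(at least one) = 1 − 0.95^k:

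- k = 5: 1 − 0.95⁵ = 22.6%
- k = 4: 1 − 0.95⁴ = 18.5%

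**All three regressions.** The protocol requires all three to be significant, so the figures above are upper limits for declaring a false mediator. This was simulated with five independent baseline variables, each with within-arm correlation r with TQ change, and a treatment effect of 8.72/13.72 SD. There were 8,000 runs per setting, and the bootstrap was not simulated. The article gives no value of r, so a range is shown.

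| Assumed r | 37 per group | 100 per group |
|---|---|---|
| 0 | 1.1% | 1.2% |
| 0.2 | 6.8% | 18.2% |
| 0.3 | 11.2% | 21.9% |
| 0.4 | 15.2% | 21.1% |

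At 100 per group with r of 0.3 or more, the first and third regressions are almost always significant, so the result approaches the 22.6% of the second regression.

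**Which mediators can be used at week 9.** The randomised contrast with an untreated control exists only up to week 9. For the delayed group at that point (its start of therapy) the Abstract lists only TFI, TQ, VAS loudness and the TMD pain screener. Table 2 gives PPT and mouth opening as researcher-measured. The Randomisation procedure ties the blinded examination to 18 weeks after each patient starts therapy. The design figure is not shown. The text at hand therefore does not establish whether PPT and mouth opening are measured in the untreated delayed group at week 9.

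**The case against.** Mediation is a secondary aim, and neither the primary TQ test nor its sample size depends on it. That stands.

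A reader might infer that the mechanism question cannot be answered at all. The article does not support this: the three mediators named in the Discussion are also secondary outcomes in Table 2, so they are analysed under either wording. The extra candidates add false leads without removing the real ones.

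A reader might also take 23% as the chance of declaring a false mediator, or extend it to 1 − 0.95¹³ = 49% for all 13 outcomes against 1 − 0.95³ = 14% for the Discussion's three. These are rates for the second regression only. The 49% and 14% further assume that treatment affects none of the measures, TMD pain included, which is not a sensible premise here. A false mediator must also predict TQ change, and without that the rate is about 1%.

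Excluding VAS loudness or the psychoacoustic measures because they describe tinnitus would be a judgement. The article defines mediators broadly, and loudness could lie on the path to distress. Replacing the three-step approach with inference on the indirect effect alone is likewise a preference of method. The bootstrap sentence is loose wording in a condensed article, but its stated purpose is still not what a bootstrap does: it expresses uncertainty in the indirect effect and removes neither chance imbalance nor multiplicity.

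The conflict between the two lists and the inclusion of baseline-only variables remain. The article states both rules outright, so neither is detail left to an analysis plan.

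**Conclusion.** The point holds for the mediation analysis. The Statistics section and the Discussion give incompatible mediator lists, and the wider one includes five variables (four if the TFI is measured later) that cannot be mediators because Table 2 records them only before treatment.

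The size is moderate and depends on assumptions. At least one of the five passes the second regression with probability about 23% (18.5% for four) under independence. At least one passes all three with probability about 1% if none is prognostic, and roughly 7–15% at 37 per group or 18–22% at 100 per group for assumed correlations of 0.2–0.4. Correlation among the variables, separate testing of subscales and items, and the bootstrap would all alter these figures. The contradiction and the logical fault do not depend on them.

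**What to change.** - State one mediator list, identical in the Statistics section and the Discussion, restricted to variables measured after baseline in both arms while the delayed group is still untreated.
- Before fixing that list, confirm from the visit schedule whether PPT and mouth opening are measured in the delayed group at week 9.
- Remove the baseline-only variables from the mediation analysis and use them for the prognostic-indicator aim. Label that work exploratory or state how multiplicity is handled: five unadjusted tests at 0.05 would carry the same 22.6% chance of a false finding there.
- Reconcile the TFI timing between the Abstract, Table 2 and the Discussion.
- Describe the bootstrap as giving a confidence interval for the indirect effect.

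The list correction changes wording only and needs no new patients or data. The cost is fewer candidate mediators. If the clinical tests are not done in the delayed group at week 9, the TMD pain screener may be the only one left of the Discussion's three.

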## Discussion

The aim of this study is to investigate the effect of a conservative TMJ treatment on several tinnitus and TMJ-related parameters. Currently, the studies that investigated the effect of TMJ therapy on somatic tinnitus have a high risk of bias, mainly due to a lack of statistical analyses between groups and before-after treatment, incomplete presentation of the data and selective reporting [42]. Additionally, risk of bias is present due to a lack of information about the blinding process of the subjects, therapists and investigators. Blinding of the subjects and therapists is always a hurdle in studies investigating therapy treatment and is hard to overcome. Therefore, blinding of the assessor, who performs the follow-up measurements and data processing, is even more crucial. In this study, a high-quality methodological design will be used by performing a prospective comparative delayed design with a blinded evaluator at baseline, end of therapy, and 9 and 18 weeks after therapy.

Furthermore, earlier studies that investigated the effect of conservative TMJ treatment on somatic tinnitus did not always match the evidence-based practice for TMJ treatment. In patients with tinnitus as well as TMD or oral parafunctions, it is thought that tinnitus improvement can be achieved by improving the TMJ complaints. Therefore, it is necessary to use the best available TMJ treatment option in order to gain maximal improvement in tinnitus complaints. For example, Bösel et al. [43] applied self-therapy next to splint therapy, although Tuncer et al. [44] found that physiotherapy performed by a therapist in combination with home physical therapy was more effective in terms of TMD pain and pain-free maximal mouth opening than home physical therapy alone.

Additionally, the multifactorial aetiology of TMD should be considered. Studies have proven that TMD patients show increased somatisation, stress, anxiety and depression compared to healthy individuals [45, 46]. Therefore, there is a need for multimodal therapies, incorporating behavioural and educational approaches, which seem to offer more benefit than a single-treatment program in patients with high psychological distress [47].

In this respect, we decided to use a multimodal treatment in the current study, which is provided by dentists and physical therapists. All physical therapists are trained in the treatment protocol by the researchers (guided referral) and will adjust the treatment modalities to the needs of the individual patient.

Currently, the clinical evaluation of somatic tinnitus is based on a generally accepted set of anamnestic criteria [24]. According to these criteria, somatic tinnitus is suspected when the tinnitus is associated with an evident history of head or neck trauma, some manipulation of the teeth, jaw or cervical spine, recurrent pain episodes in head, neck or shoulder girdle, temporal coincidence of onset or increase of both pain and tinnitus, increase of tinnitus during inadequate postures when resting, walking, working or sleeping, or intense bruxism periods during the day or night. These criteria imply a temporal and mechanical association between TMJ or cervical spine dysfunction, and tinnitus complaints. If one of the abovementioned criteria is present, somatic tinnitus is suspected and further evaluation is warranted. Other studies have described the presence of modulation of tinnitus during forceful contractions of the neck and jaw musculature [5, 48]. However, these tests also elicit a sound perception in 65% of an asymptomatic control group without tinnitus complaints, which makes modulation tests minimally useful for diagnosing somatic tinnitus. Therefore, we apply a combination of thorough ENT, audiological and temporomandibular assessments combined with the abovementioned diagnostic criteria to diagnose somatic tinnitus. While all objective causes of tinnitus are excluded, we aim to include patients with a co-existence of severe subjective tinnitus and temporomandibular complaints in order to include patients who can potentially benefit from the treatment.

To obtain a detailed view on the patients’ subjective tinnitus complaints, the TFI will be used [33]. Since the responsiveness of this questionnaire is limited due to important floor effects on more than half of the questions, this questionnaire will not be used to evaluate treatment effect [49].

To improve the quality of patient care, it is important that clinicians are able to identify who has a high likelihood for a positive treatment effect and who is at risk of poor recovery. Therefore, we aim to identify prognostic indicators to provide arguments why someone might benefit from TMJ treatment or not. This can reduce the current trial and error strategy and thus avoid patient frustration and unnecessary reimbursement of unsuccessful therapies.

To date, no prognostic indicators are available for the effect of TMD treatment on tinnitus. However, an earlier study in cervicogenic somatic tinnitus showed that patients with low-pitched tinnitus, that co-varies with the neck complaints and increases during inadequate postures, has the best prognosis after cervical spine treatment [50]. Rollman et al. [51] studied a variety of prognostic indicators for TMD pain in general and found that a longer duration of the TMD-pain complaint, a higher number of attended care practitioners and higher degree of hindrance on function, negatively predicted 6-month improvement. It is unclear to what extent these prognostic indicators can be transferred to our population of patients with tinnitus as a main complaint; consequently, we aim to identify prognostic indicators for the effect of TMJ treatment on tinnitus.

To understand the working mechanism behind TMJ treatment for somatic tinnitus it is necessary to identify variables that have an effect on the main outcome variable (TQ). Knowing that a treatment is beneficial for patients is important, but knowing how it works adds to the understanding and acceptance of the findings among clinicians. Therefore, we also aim to identify possible mediating factors, i.e. factors that contribute to the therapeutic effect. The underlying idea is that TMJ contributes to somatic tinnitus. Consequently, variables that measure TMJ parameters are used as potential mediators; these are TMJ pain via the TMD pain screener, pain sensitivity as measured via PPT and mouth opening.

Since patients are recruited in a tertiary centre with long waiting lists, it would be unethical to include patients in a placebo group receiving no treatment at all. Therefore, this study is designed as a randomised controlled trial with a delayed treatment design. In this type of design, one group of patients will receive 9 weeks of treatment immediately, while the delayed-start group will receive the standard information and advice about tinnitus. After 9 weeks, the delayed-start group will also receive the TMD therapy.

To date, the inclusion of the pilot study is completed. The follow-up results are expected by the end of December 2017. Afterwards, a sample size recalculation will be performed.

This study is the first to investigate the effect of a state of the art conservative TMJ treatment protocol on patients with somatic tinnitus using a prospective comparative delayed design and blinded evaluator for baseline, end of therapy, and 18 and 27 weeks after therapy (Additional file 1).

### Trial status

The study is in the recruitment phase.

## Abbreviations

CN: cochlear nuclei
ENT: ear-nose-throat
HADS: Hospital Anxiety and Depression Scale
HQ: Hyperacusis Questionnaire
PPT: pain pressure threshold
TFI: Tinnitus Functional Index
TMD: temporomandibular disorders
TMJ: temporomandibular joint
TQ: Tinnitus Questionnaire
VAS: Visual Analogue Scale
